# Sintilimab plus fruquintinib with or without radiotherapy for third-line treatment of colorectal cancer with liver metastases: study protocol for a randomized controlled, multicenter phase II trial

**DOI:** 10.3389/fimmu.2026.1622828

**Published:** 2026-05-12

**Keywords:** fruquintinib, immunotherapy, liver metastases, liver-directed radiotherapy, metastatic colorectal cancer, sintilimab

## Abstract

**Background:**

Metastatic colorectal cancer (mCRC) has limited treatment options beyond the second-line. Accumulating evidence has reported that liver metastases harbor a greater abundance of immunosuppressive cells relative to primary tumors. However, about 70% of mCRC patients have liver metastases, which worsen prognosis and reduce immunotherapy benefits. Local therapies, such as liver-directed radiotherapy, have shown promise in reducing tumor burden and improving survival.

**Methods:**

This phase II trial aims to evaluate the efficacy and safety of sintilimab combined with fruquintinib, with or without liver-directed radiotherapy, versus fruquintinib alone in the third-line treatment of colorectal cancer with liver metastases (CRCLM). Patients aged 18–75 years with microsatellite stable CRCLM who have received first- and second-line therapies will be randomized 3:3:2 into intervention, control, and standardized treatment groups. Patients in the intervention group will be given sintilimab plus fruquintinib in combination with liver-directed radiotherapy. For liver oligometastases, stereotactic body radiation therapy (SBRT) will be performed with a dose of 40–50 Gy/5 F, 60–70 Gy/10 F, or 65 Gy/13 F. For multiple liver metastases, SBRT plus low-dose radiation therapy (LDRT) will be performed. The appropriate lesions will be selected to receive SBRT with a dose of 40–50 Gy/5 F, 60–70 Gy/10 F, or 65 Gy/13 F, and the remaining liver lesions will undergo LDRT at a total dose of 1–10 Gy with 0.5-2.0 Gy/F. Patients in the control group will be treated with sintilimab plus fruquintinib, and patients in the standardized treatment group will be treated with fruquintinib only. The primary endpoint is PFS and secondary endpoints are objective response rate, disease control rate, OS, and safety.

**Discussion:**

We hypothesize that combining sintilimab with liver-directed radiation therapy on the basis of fruquintinib will enhance disease control and prolong survival compared to treatment with fruquintinib plus sintilimab alone.

**Clinical Trial Registration:**

clinicalTrials.gov, identifier (NCT06356584).

## Introduction

1

Early symptoms of colorectal cancer (CRC) are not obvious, and 25% of patients have distant metastasis at diagnosis, which cannot be cured by surgery alone (1). For metastatic CRC (mCRC), the progression-free survival (PFS) is about 10–12 months for first-line and 6 months for second-line therapy (2, 3). After failure of first- and second-line treatments, third-line and beyond therapies remain suboptimal. Currently, third-line therapies of mCRC recommended by major guidelines include fruquintinib, regorafenib, and trifluridine-tipiracil (TAS-102) with or without bevacizumab (4–6). Although extensive data for third-line treatment of mCRC have been published, the results show that the prognosis remains poor, with a median PFS (mPFS) of only 3.2-5.6 months (7–12). There is an urgent need to find novel therapies.

At present, immune checkpoint inhibitors (ICIs), such as programmed death-1 (PD-1) monoclonal antibodies, have achieved great success in clinical practice; however, for mCRC, the population benefiting from ICIs is still limited to about 5% of patients with high microsatellite instability (MSI-H) (13). The microsatellite stable (MSS) type, which accounts for 95% of mCRC, shows limited response to immunotherapy. Combination regimens are a major focus of immunotherapy research, and immunotherapy combined with targeted therapy holds great promise (14). Clinical studies have shown that targeted drugs combined with ICIs hold promising prospects for improving survival outcomes for MSS mCRC patients (15–17).

Liver metastases significantly impair the response of mCRC to immunotherapy. Yu et al. showed that liver metastases can exploit immune tolerance mechanisms, leading to CD8^+^ T cell depletion (18). Lee et al. described another mechanism—the regulation of regulatory T cell recruitment and the activation and modulation of CD11b^+^ monocytes at the primary tumor site (19). Multiplex immunohistochemistry analysis within the REGONIVO and LENPEM cohorts revealed that liver metastases have more immunosuppressive cells and fewer CD8^+^ T cells compared to primary tumors (20). Adding local therapies to systemic therapy can effectively reduce tumor burden and may contribute to better survival (21, 22). Radiotherapy, with high local control rates and a favorable safety profile, is one of the most important local treatment modalities and provides substantial clinical benefits to patients. Notably, liver-directed radiotherapy combined with immunotherapy can restore immune cell function, enhance anti-cancer immunity, and increase sensitivity to anti-PD-L1 therapy (18).

Herein, the aim of this study is to evaluate the efficacy and safety of fruquintinib plus sintilimab combined with liver-directed radiotherapy versus fruquintinib plus sintilimab for third-line treatment of CRC with liver metastasis (CRCLM).

## Methods

2

### Objectives

2.1

The aim of this study is to evaluate the efficacy and safety of sintilimab in combination with fruquintinib with or without liver-directed radiotherapy for the third-line treatment of CRCLM.

### Study design

2.2

This study is a randomized, controlled, multicenter phase II clinical trial, which will be conducted at the Shandong Cancer Hospital and Institute. The study has been authorized by the ethics committee of Shandong Cancer Hospital and Institute (No. SDZLEC2024-078-01) and all patients will provide written informed consent before enrollment. The trial has been registered on the ClinicalTrials.gov under the registration number NCT06356584 (June 21, 2025).

### Study population

2.3

#### Inclusion criteria

2.3.1

Men or women between the ages of 18 and 75 years old.Eastern Cooperative Oncology Group Performance Status (ECOG PS) Score from 0 to 2.Have histopathologically confirmed colorectal adenocarcinoma with liver metastases according to the *American Joint Committee on Cancer 8th edition* classification of malignancies.*RAS* and *BRAF* gene mutant or wild types, MSS type.Previously received standard first- and second-line systemic anti-cancer therapy.Have at least one measurable lesion as defined by RECIST 1.1 standards.Tumor samples can be obtained for biomarker evaluation.Expected survival ≥ 3 months.Normal major organ function two weeks prior to enrollment.

#### Exclusion criteria

2.3.2

Diagnosis of a malignancy other than CRC within the past 3 years (excluding radically treated basal cell carcinoma of the skin, squamous epithelial carcinoma of the skin, and/or radically resected carcinoma *in situ*).MSI-H tumors.History of treatment with fruquintinib or regorafenib and immunotherapy.Liver-directed radiotherapy within 2 weeks prior to enrollment.Treated with other investigational agents or with investigational devices within 4 weeks prior to enrollment.Being allergic to active ingredients or excipients of sintilimab or fruquintinib.Central nervous system metastases and/or carcinomatous meningitis.Pregnant or breastfeeding women.Any serious or uncontrolled systemic disease.

### Randomization and blinding

2.4

All included patients will be randomized into intervention, control, and standardized treatment groups in a 3:3:2 ratio using a computer-generated random sequence by a clinical research assistant. This study is an open-label trial, so participants, care providers, and investigators will not be blinded.

### Interventions

2.5

The study flow is presented in **Figure 1**. Patients in the intervention group will be given sintilimab (200 mg, IV, D1, once every 3 weeks) plus fruquintinib (5 mg, po, D1-14, once every 3 weeks) in combination with liver-directed radiotherapy. A 21-day treatment cycle of sintilimab (200 mg, IV, D1, once every 3 weeks) will be given intravenously on day 1 of each cycle, and fruquintinib will be given on days 1 through 14 of each cycle. The radiologist will determine the radiation division pattern based on the location and volume of the liver metastases. For liver oligometastases, stereotactic body radiation therapy (SBRT) will be performed with a dose of 40–50 Gy/5 F, 60–70 Gy/10 F, or 65 Gy/13 F. For multiple liver metastases, SBRT plus low-dose radiation therapy (LDRT) will be performed. The appropriate lesions will be selected to receive SBRT with a dose of 40–50 Gy/5 F, 60–70 Gy/10 F, or 65 Gy/13 F, and the remaining liver lesions will undergo LDRT at a total dose of 1–10 Gy with 0.5-2.0 Gy/F. One or more appropriate lesions will be selected by the physician based on the surrounding organs at risk. Extrahepatic lesions will not receive radiation therapy. Liver radiotherapy will be administered within 1 week of initiating immunotherapy. For patients receiving a 5-fraction regimen, the volume receiving ≥15 Gy will be limited to <700 cc and the Dmean will be <16 Gy. For those treated with 10 or 13 fractions, the volume receiving ≥24 Gy will be limited to <700 cc and Dmean will be <24 Gy for patients with Child-Pugh class A, and the limits will be V18Gy <700 cc and Dmean <18 Gy for patients with Child-Pugh class B. **Figure 2** shows an example of target area delineation and radiation dose distribution for two patients.

**Figure 1 f1:**
[figure not shown]
Study flow of the present study. In this phase II study, we will assess the efficacy and safety of sintilimab and fruquintinib combined with liver-directed radiation therapy versus sintilimab and fruquintinib for the third-line treatment of colorectal cancer with liver metastases.

**Figure 2 f2:**
[figure not shown]
An example of target area delineation and radiation dose distribution for two patients. The top row **(A–C)** represents a patient with liver oligometastasis receiving 40 Gy/10 F irradiation, with the images displayed in axial, coronal, and sagittal planes. The bottom row **(D–F)** represents a patient with multiple liver metastases receiving 10 Gy/5 F irradiation, with the images displayed in axial, coronal, and sagittal planes.

Patients in the control group will be treated with sintilimab plus fruquintinib. A 21-day treatment cycle of sintilimab (200 mg) will be given intravenously on day 1 of each cycle, and a 21-day treatment cycle of fruquintinib (5 mg) will be given orally on days 1 through 14 of each cycle. Patients in the standardized treatment group will be treated with fruquintinib (5 mg) only, and a 21-day treatment cycle of fruquintinib will be given on days 1 through 14 of each cycle.

For all included patients, CT scans will be repeated every 12 weeks during the treatment to evaluate the efficacy, and the regimen will be continued if the response is evaluated as complete response (CR), partial response (PR), stable disease (SD), or non-progressive disease (PD). Sintilimab is administered for no more than 2 years. No dose adjustments of sintilimab are permitted throughout the study. Fruquintinib is continued until toxicity is intolerable, PD, or death.

### Follow-up

2.6

A safety follow-up will be conducted within 30 days (± 7 days) after the last dose of the study drug, or prior to initiating a new anti-cancer therapy, whichever occurs first. After safety follow-up, subjects will enter survival follow-up, where subjects will be contacted every 90 days (± 7 days) to obtain comprehensive information regarding survival status and any subsequent systemic anti-cancer therapies. Long-term follow-up will continue until the end of the study, death of the subjects, loss to follow-up, withdrawal of consent, or early termination of the study at the option of the sponsor. The details of the patient assessment schedule are described in **Supplementary Table 1**.

### Tumor response assessment

2.7

#### Baseline tumor imaging

2.7.1

The first tumor imaging at screening must be conducted within 28 days prior to the first administration of the study drug and will serve as the basis for the oncology assessment during the screening period. The imaging typically includes contrast-enhanced CT or MRI of the chest and abdomen. Pelvic CT or MRI, cranial MRI, and whole-body bone imaging are also required at baseline. PET/CT is also acceptable as a screening method for baseline evaluation.

#### Tumor imaging during the study

2.7.2

Tumor imaging will be evaluated every 12 weeks (± 7 days) starting from the first dose. Unscheduled imaging evaluations will be conducted at any time if the subject experiences clinical disease instability during the study.

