#### Primary outcome

2.9.1

The primary outcome of this study is PFS, defined as the time from treatment initiation to first radiological disease progression according to the Response Evaluation Criteria in Solid Tumors version 1.1 (RECIST v1.1) or death, whichever occurs first. The radiologic evaluation will be performed every 12 weeks (± 7 days) by unblinded investigators and centrally by an independent group of radiology experts, beginning after treatment initiation.

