#### Sample size estimation

2.13.1

As reported in the literature (15), the mPFS of CRCLM subgroup in the control group is 1.8 months (regorafenib + nivolumab). The mPFS in the intervention group is estimated to be 3.7 months with a hazard ratio (HR) of 0.5. With a one-sided significance level of 0.05 (power of test of 80%), case enrollment of 18 months and follow-up of 12 months, and assuming a 5% dropout rate, a 1:1 enrollment ratio for the intervention and control groups will require sample sizes of 24 and 23 cases, respectively. In addition, a standardized treatment group with a sample size of 15 cases will be set up, totaling 62 cases. These three groups will be randomly enrolled in a 3:3:2 ratio. It is worth noting that the standardized treatment group is mainly used for descriptive comparisons and safety references, and is not included in the scope of the main hypothesis tests. The comparison between the intervention group and the control group is designated as the primary analysis.

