#### Statistical analysis methods

2.13.2

Clinical characteristics and safety outcomes will be summarized using descriptive statistics. Unless otherwise stated, continuous data will be statistically described using mean (± standard deviation) or median (minimum, maximum). Categorical data will be statistically described using frequencies (percentages). Cox proportional hazard models will be used for univariate and multivariate survival analyses, with HRs and 95% confidence intervals (CIs) calculated. Subgroup analyses will be conducted by the characteristics of patients and liver metastases (liver oligometastases or multiple liver metastases). Both the intention-to-treat (ITT) population and the per-protocol population will be used for efficacy and safety analyses. The worst-case imputation and complete-case analysis will be performed as sensitivity analyses to handle the missing data and dropouts (24). The SAS 9.2 (or higher) will be used for statistical analyses, using a one-sided 0.05 hypothesis test of superiority, and 95% CIs and *P* values will be reported for group comparisons.

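### The 12-week scan interval exceeds the planned 1.8-month control median, so observed PFS medians will follow the scan dates and the stated 80% power, about 70–75% on this grid, makes no allowance for it

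*Protocol article*

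**What the plan says.** Protocol section 2.7.2 (Tumor imaging during the study) sets the calendar: "Tumor imaging will be evaluated every 12 weeks (± 7 days) starting from the first dose". Sections 2.5 and 2.9.1 repeat the 12-week interval. Section 2.7.2 also permits earlier scans: "Unscheduled imaging evaluations will be conducted at any time if the subject experiences clinical disease instability during the study".

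Section 2.9.1 (Primary outcome) makes PFS the primary endpoint, "defined as the time from treatment initiation to first radiological disease progression" by RECIST 1.1, or death if that comes first.

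Section 2.13.1 (Sample size estimation) states that "the mPFS of CRCLM subgroup in the control group is 1.8 months", citing a regorafenib plus nivolumab study, and continues: "The mPFS in the intervention group is estimated to be 3.7 months with a hazard ratio (HR) of 0.5". From these figures, with a one-sided 5% level, 80% power, 18 months of enrolment, 12 months of follow-up and 5% dropout, it arrives at 24 intervention and 23 control patients. It makes no reference to the scan interval.

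On method, section 2.13.2 says: "Cox proportional hazard models will be used for univariate and multivariate survival analyses". It also specifies a one-sided 0.05 superiority test. It names neither a log-rank test nor a method for ties or interval censoring.

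**The concern.** Progression is a date on a scan. If the first scheduled scan comes a month after the planned control median, most control progressions will be recorded at that scan, whenever they actually occurred. Two things are at stake.

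First, the reported medians would describe the calendar. A control median near 2.8 months could be mistaken for an improvement on 1.8 months when the two are consistent.

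Second, the power calculation gives no sign of allowing for coarse dating. Lumping events at weeks 12 and 24 discards information on ordering, and some ways of handling the ties also pull the hazard ratio toward 1.

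**Working it through.** **Inputs.** From the protocol: scan interval 12 weeks ± 7 days (2.7.2, 2.9.1); medians 1.8 and 3.7 months, HR 0.5, one-sided 0.05, power 80%, accrual 18 months, follow-up 12 months, dropout 5%, 24 + 23 patients (2.13.1). Assumed: exponential PFS, proportional hazards, 1.8 months taken as the underlying median, and no dropout in the simulations. The share of events dated between scheduled scans is not given, so it is varied over 0%, 25% and 50%.

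**1. The plan's own sample size.** The medians give HR = 1.8/3.7 = 0.486. Schoenfeld events = 4 × (1.645 + 0.842)² / (ln 0.486)² = 24.73 / 0.519 ≈ 47.6, so 48 (52 for HR 0.5). Nearly every patient has an event within the planned follow-up, so N is about 48.4 before dropout and 48.4 / 0.95 ≈ 51 after it. Other standard formulas at HR 0.486 give 55–56. The stated 47 is not reproduced. It lies close only to the Schoenfeld figure without dropout. This shortfall has nothing to do with the scan grid and must be kept apart from it.

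**2. Events before the first scheduled scan.** 12 weeks = 84 / 30.4375 = 2.76 months, and S(t) = 0.5^(t / median).

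| | Control (1.8 mo) | Intervention (3.7 mo) |
|---|---|---|
| S(12 wk) | 0.346 | 0.596 |
| S(24 wk) | 0.119 | 0.356 |
| Event before week 12 | 65% | 40% |

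**3. Observed medians.** If progression is dated only at scheduled scans, the control curve falls below 50% at the first scan (2.76 months) and the intervention curve at the second (5.52 months). In simulation with 23 controls and ± 7-day scan dates, the typical control median was 2.89 months with no events dated exactly, 2.86 with 25% and 2.76 with 50%. A control median of 1.9 months or less occurred in 0%, 0% and 0.5% of runs. In separate runs without the ± 7-day spread, the intervention median stayed at 5.5 months with 0% or 25% exact and fell to about 4.8 with 50%.

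**4. Power and hazard ratio, 24 vs 23, one-sided 0.05.** Simulated power:

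| Event dating | Method | True HR 0.486 | True HR 0.5 |
|---|---|---|---|
| Exact | Log-rank | 77% | 74–75% |
| 12-week grid, fully tied | Log-rank | 75% | 73% |
| 12-week grid, fully tied | Cox, Efron | 73% | 70% |
| 12 weeks, ± 7-day dates | Log-rank | 72% | 70–71% |
| 12 weeks, ± 7-day dates | Cox, Efron | 72% | 70% |
| 12-week grid, fully tied | Cox, Breslow | 44% | 41% |

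With true HR 0.486, the large-sample estimate is 0.50 (Efron, on the grid or with ± 7-day dates), 0.51 (Breslow with ± 7-day dates), 0.615 (Breslow, fully tied) and 0.486 (grouped-time complementary log-log model). That grouped model had 78% power, with simulated one-sided type I error of 5.7%.

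Dating a random 25% or 50% of events exactly did not restore the power. Log-rank gave 71–73% at HR 0.486 and 68–70% at HR 0.5.

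**5. Size needed for 80%.** By log-rank at HR 0.486, about 26 per arm suffice with exact times (simulated 80.7%). With 12-week scans and ± 7-day dates the number is about 28–29 per arm (79.6% at 28, 82.0% at 30). Both figures are before dropout.

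**The case against.** The strongest reply is that the grid does limited harm to the randomised comparison. All arms share one schedule, the primary analysis is intervention against control, and no test against 1.8 months is planned. Deaths count as events, unscheduled scans are allowed, and the ± 7-day window separates most ties. All of this stands. It is why the hazard ratio moves by only about 0.02 and the grid costs only about 2–6 points of power. It also rules out saying that the planned medians can never be observed, although earlier dating of even half the events seldom brings the control median near 1.8.

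A reader might infer something stronger: that a Cox analysis here will pull the hazard ratio to about 0.6 and cut power to about 45%. The protocol does not support that. Those figures need Breslow ties on fully tied visit times. Section 2.13.2 names no tie method, and that choice is commonly left to a statistical analysis plan, which is not shown. With ± 7-day dates even Breslow gives about 0.51.

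Nor can the whole gap to 80% be charged to the scans. About 3–6 points of it are there with exact times.

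What the reply leaves untouched is that the interval and the planning median do not fit together, and that the stated power does not reflect the design.

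**Conclusion.** The point holds at moderate size. On the protocol's own planning figures the scan interval is about one and a half times the control median (2.76 / 1.8 = 1.53). The observed medians will track the scan calendar, at about 2.8 and 5.5 months, and should not be compared with the 1.8-month benchmark. Power is about 70–75% with 12-week scans and sound handling of ties, against a stated 80%. Of that gap, about 2–6 points come from the grid and the rest from the separate sample-size shortfall. Attenuation of the hazard ratio is slight, and severe attenuation is only a worst case under an unstated analysis choice.

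The figures assume exponential PFS, proportional hazards and no dropout. Dropout would lower power a little further. The protocol does not give the scan schedule behind the 1.8-month figure. If that median was itself shaped by scan dates, comparing medians would be less secure still.

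**What to change.** - Restate the power for 24 vs 23 patients under the 12-week grid. If 80% is to be kept, restate the sample size: about 28–29 per arm before dropout, or 28 / 0.95 to 29 / 0.95, about 30–31 per arm, after 5% dropout.
- Name the log-rank test as the primary PFS test.
- Estimate the hazard ratio with an interval-censored or grouped-time proportional hazards model, or with Cox using Efron or exact ties. Exclude Breslow on tied visit times.
- Report PFS rates at weeks 12 and 24 beside the medians, and do not set the medians against 1.8 months.
- The sponsor must reconcile the scan interval with the planning median. The analysis changes above do not depend on how that is done.

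The analysis changes need no extra data and only standard methods. Their costs are a less familiar model for the hazard ratio and a less favourable stated power. The grouped model is also imperfect at this size. Its simulated type I error was about 5.7–6%, and its median estimate was 0.457 for a true 0.486, so the log-rank should remain the test. No analysis method frees the observed medians from the scan dates.
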